### Participant timeline {13}

The SPIRIT participant timeline for the study can be seen in Table 1.

### Sample size {14}

Using GPower 3.1 (University of Kiel, Kiel, Germany), this experiment is a factorial design, and the parameters required for this experiment are not found in previous studies. Based on the expected results of the experiment, a small effect size of 0.2 [15], two-sided A = 0.05, test power (1-β) of 0.9, and the F-test are taken to calculate the sample size of 220 cases. To compensate for an estimated 20% loss to follow-up, the final total sample size is 264 cases.

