## Statistical methods

### Statistical methods for primary and secondary outcomes {20a}

Data will be analyzed applying SPSS 23.0 (IBM, Chicago, IL, USA). Data will be expressed as mean ± standard deviation or as *n* (%) in the case of categorical data, and differences between the four groups will be assessed for significance using the chi-squared test in the case, analysis of variance in the case, or non-parametric rank-sum test in the case of skewed continuous data. Differences between different time points within each group will be assessed for significance using generalized estimation equation. These models will include intervention variables, time as a categorical variable represented by dummy variables, the interaction between intervention and time, and baseline values. Differences associated with *P* < 0.05 will be considered significant.

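### The sample size of 220 does not follow from the inputs printed in section {14}, so the stated 90% power is not supported by them

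*Protocol article*

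**What the plan says.** Section {14} of the protocol article says that G*Power 3.1 was used and that "this experiment is a factorial design". It gives "a small effect size of 0.2 [15], two-sided A = 0.05" and then "test power (1-β) of 0.9, and the F-test are taken to calculate the sample size of 220 cases". The total is raised to 264 for an expected 20% loss to follow-up. The section does not say whether 0.2 is f, d or another measure. It also gives no numerator degrees of freedom, number of repeated measurements or correlation.

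Section {20a} says that "differences between the four groups will be assessed for significance", with analysis of variance among the listed tests. It adds generalized estimating equations for time points within groups, in models that include baseline values. Allocation to the four groups is equal (section {8}). HbA1c is measured at baseline, 3 months and 6 months (sections {12} and {18a}), and the abstract places the primary outcome at 6 months.

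**The concern.** A sample-size paragraph that prints its inputs and its answer should let a reader get from one to the other. Here the usual reading of an ANOVA F-test with an effect size of 0.2 leads to a clearly larger number than 220, whether the test is a factorial main effect or a comparison of all four groups.

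What is at stake is how a null result would be read. The Discussion cites a systematic review in which only one of 11 studies found an HbA1c difference related to app use, so a null finding is a realistic prospect. It would be judged against a claimed type II error of 10%, when the printed inputs give 16% or 31% at 220 participants.

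**Working it through.** **Inputs.** From section {14}: effect size 0.2, alpha 0.05 two-sided, power 0.90, F-test. From section {8}: four groups, equal allocation. Assumption: 0.2 is Cohen's f. The numerator df is not stated, so both candidates are taken: 1 for a main effect or the 2×2 interaction, 3 for the four-group test.

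**Formula.** In a fixed-effects ANOVA with k = 4 groups, the F statistic is noncentral F with df1, df2 = N − 4 and λ = f²N. Power is the probability that it exceeds the central F critical value at alpha = 0.05. The required N is the smallest with power of at least 0.90.

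**Attempt to reproduce 220.**

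| Test | Required N | In four equal groups |
|---|---|---|
| 1 df | 265 | 268 |
| 3 df | 359 | 360 |

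Neither gives 220. As a cross-check, f = 0.2 for a balanced two-level factor is d = 2 × 0.2 = 0.4, and the normal-approximation two-sample formula gives 264 in total.

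**Power at f = 0.2.** Loss of 20% from 264 leaves 264 × 0.8 = 211.2, so 211.

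| N analysed | λ = 0.04 × N | 1 df | 3 df |
|---|---|---|---|
| 211 | 8.44 | 0.824 | 0.671 |
| 220 | 8.80 | 0.840 | 0.692 |
| 264 (no loss) | 10.56 | 0.899 | 0.779 |

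For 220 to give 90% power, f would have to be about 0.220 (1 df) or 0.256 (3 df).

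**Other readings tried.**
- *One-sided 5% level (F-test at alpha 0.10, 1 df):* N = 216. This is close, but the text says two-sided.
- *Repeated measures, between-groups effect, four groups, 3 df:* λ = f²N·m / (1 + (m − 1)ρ), with m measurements and correlation ρ. For m = 3 and ρ = 0.4 the multiplier is 3/1.8 = 1.667. For m = 2 and ρ = 0.2 it is 2/1.2 = 1.667. Both give a minimum N of 217, which is 220 when rounded up to four equal groups of 55. For m = 3, ρ = 0.3 gives 193 and ρ = 0.5 gives 241 (244 in equal groups).
- *0.2 read as f²:* N = 55 (1 df) or 75 (3 df).

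**Baseline-adjusted analysis at 211 completers.** Here λ = f²N / (1 − ρ²), df2 = N − 5, and ρ is the assumed correlation between baseline and 6-month HbA1c.

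| ρ | λ | 1 df | 3 df |
|---|---|---|---|
| 0.4 | 8.44/0.84 = 10.05 | 0.88 | 0.75 |
| 0.5 | 8.44/0.75 = 11.25 | 0.92 | 0.81 |

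**The case against.** The strongest reply is that section {14} says only F-test and does not say which one. HbA1c is measured three times and section {20a} plans a longitudinal model, so a repeated-measures F-test would fit the design. With three measurements and a correlation of 0.4 it gives exactly 220 in four equal groups. The article condenses a fuller protocol, and an assumed correlation is the kind of detail that may stand there.

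Much of this stands. It rules out saying that no F-test calculation yields 220. It also rules out the stronger inference a reader might draw, that the 90% power claim is simply false. That would require knowing the metric, the test and its degrees of freedom, and the document gives none of them.

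It does not remove the point. The paragraph offers a set of inputs as the source of 220, and they do not produce it on the fixed-effects reading. The repeated-measures reading needs two further inputs, and the answer is sensitive to them. It also tests a group effect averaged over the measurements. If those are the three planned visits, one of them precedes randomisation, while the abstract places the primary outcome at 6 months.

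A reader might also infer from the word small that a standardised difference of d = 0.2 was meant, which would need 1053 participants on the 1-df test (f = 0.1). That is hypothetical: the text does not define the metric, and the source cited for it is not available here.

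Finally, it can be said that adjusting for baseline restores the target. That holds for the 1-df test at an assumed correlation of 0.5, but not at 0.4, and not for the 3-df test at either value.

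**Conclusion.** The point holds in limited form: 220 does not follow from the inputs as printed, and 90% power is not supported by them. On the fixed-effects reading, the expected 211 completers fall about 8 percentage points short for a 1-df main effect (82%) and about 23 points short for the four-group test (67%). Reaching 90% would need 265 or 359 analysed, which is 265/0.8 ≈ 332 or 359/0.8 ≈ 449 enrolled.

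These sizes rest on reading 0.2 as Cohen's f and on an unadjusted analysis at one time point. The arithmetic is secure under those assumptions. Which calculation the sponsor actually ran cannot be told from the document.

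**What to change.** Keep 264 and rewrite section {14}:

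1. Name the effect-size metric, the effect being tested and its numerator df, consistent with the comparison in section {20a}.
2. Restate power at the expected 211 completers for that test. At f = 0.2 and without adjustment, this is 82% for a 1-df main effect or 67% for the 3-df four-group test.
3. If a repeated-measures or baseline-adjusted calculation was used, state the number of measurements and the assumed correlation, and give power over a range of correlations. For the baseline-adjusted case, the values at 0.4 and 0.5 tabulated above would serve.

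The cost is one rewritten paragraph and no extra patients. The stated power becomes less favourable: modestly for a 1-df main effect, clearly so if the 3-df test is kept.

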### Study design {8}

This will be a 2-center, factorial design, equal proportional distribution, superiority trial conducted in outpatient endocrinology clinics at two tertiary hospitals in Chengdu, China, which will be conducted from 2021 to 2023. 

In reporting the protocol for this study, we followed the SPIRIT 2013 checklist. Individuals will be randomly allocated to the Control group, Reminder group, App group, and App + Reminder group. Flow diagram of the study is shown in Fig. 1.

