### Methods in analysis to handle protocol non-adherence and any statistical methods to handle missing data {20c}

Data will be analyzed based on intentionality analysis. The extent to which data may be missing will be analyzed and examined, especially in view of the main findings of the study. Missing values are filled with the last data. For example, for participants without the 3rd month follow-up, the baseline data will be filled in. For participants with 3rd month follow-up but without 6th month follow-up, the 3rd month data will be filled in.

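### The enrolment total of 264 covers a 16.7% loss to follow-up, not the 20% the protocol says it covers

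*Protocol article*

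**What the plan says.** Sample size {14} of the protocol article contains the whole calculation. The inputs are "a small effect size of 0.2 [15]", "two-sided A = 0.05" and "test power (1-β) of 0.9". From these, in GPower, "the F-test are taken to calculate the sample size of 220 cases". The allowance for attrition follows: "To compensate for an estimated 20% loss to follow-up, the final total sample size is 264 cases".

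Two other sections bear on the point. Study design {8} describes a "2-center, factorial design, equal proportional distribution, superiority trial" with four groups, so the total should divide by four. The section on non-adherence and missing data {20c} plans an analysis by intention to treat in which "Missing values are filled with the last data": baseline stands in for a missed month-3 visit, and month 3 stands in for a missed month-6 visit.

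**The concern.** An allowance for loss to follow-up should leave the required number after the loss has occurred. Adding 20% to the required number does not do this, because the 20% is then lost from the larger, enrolled number. The stated total equals the required number plus 20%, so at the protocol's own expected loss rate the trial would fall below its own requirement. Precision on HbA1c, the primary outcome, at 6 months is at stake. So is the accuracy of a statement that readers will use to judge whether the trial was large enough.

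**Working it through.** **Inputs, all from Sample size {14}:** required number n = 220; loss d = 0.20; stated total 264. The four equal groups come from Study design {8}.

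**Step 1. Reproduce the stated total.** n × (1 + d) = 220 × 1.20 = 264. This matches exactly.

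**Step 2. Total that would leave 220 after 20% loss.** n / (1 − d) = 220 / 0.80 = 275. For four equal arms, 275 / 4 = 68.75, rounded up to 69 per arm, which gives 276. Check: 275 × 0.80 = 220.0 and 276 × 0.80 = 220.8.

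**Step 3. What 264 delivers.**
- Retained at 20% loss: 264 × 0.80 = 211.2, about 211.
- Shortfall against 220: 220 − 211 = 9, and 9 / 220 = 4%.
- Loss that 264 can absorb: 1 − 220 / 264 = 16.7%.

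Steps 1 to 3 use only the protocol's own figures.

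**Step 4. Effect on power.** This step needs assumptions. The protocol names neither the effect-size index nor the numerator degrees of freedom. I read 0.2 as Cohen's f because an F-test in GPower is used, and I show two cases: 1 df (a factorial main effect) and 3 df (a comparison of all four groups). Power = 1 − F_nc(F_crit; df1, N − 4, λ), with λ = N × f² and α = 0.05.

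| Participants with data | λ = N × 0.04 | Power, 1 df | Power, 3 df |
|---|---|---|---|
| 220 | 8.80 | 84.0% | 69.2% |
| 211 | 8.44 | 82.4% | 67.1% |
| Cost of the slip | | about 1.5 points | about 2 points |

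**Step 5. Separate the slip from the rest of the gap to 90%.** On the same reading, 90% power needs 265 participants (1 df) or 359 (3 df). Power at 220 is therefore already about 6 points (1 df) or 21 points (3 df) below 90% before any loss. That part comes from the 220 not following from its stated inputs, which is a different error.

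**The case against.** The arithmetic is not in dispute, and nothing elsewhere in the protocol corrects it. The serious objections concern how far it reaches.

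- **Carry-forward.** A reader might infer that the analysed number falls to 211. The protocol does not support this: under {20c} all 264 stay in the analysis. This objection stands against the word analysed. It does not rescue the sentence, because a baseline HbA1c entered as a month-6 value says nothing about what happened by month 6, and {14} itself treats loss as something to compensate for.
- **Partial follow-up.** Someone lost after month 3 still supplies an observed month-3 HbA1c, and the planned generalized estimating equation models include time. This also stands: 211 counts participants with observed month-6 data, not everyone with some follow-up.
- **Loss is only estimated.** A reader might infer that the trial will end with 211. It will do so only if loss reaches 20%; up to 16.7%, the 264 suffices for 220.
- **Size.** A reader might set 82.4% or 67.1% against the stated 90% and blame the attrition allowance. Step 5 shows that most of that gap exists at 220. Charging it to this slip would count the other error twice.
- **Enrolling 275.** This looks like the natural remedy, but it does not divide by four. Even 276 retains about 220, with power near 84% or 69% on this reading, so the 90% claim would remain unsupported.

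**Conclusion.** The statement that 264 compensates for 20% loss is wrong as written. The total covers 16.7%, and at 20% about 211 participants would have observed month-6 data, about 9 (4%) fewer than the protocol's own 220. This conclusion rests on no outside assumption.

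The statistical cost is small: about 1.5 points of power (1 df) or 2 points (3 df), if 0.2 is Cohen's f. The slip does not bias the treatment comparison and does not touch the outcome or the analysis method. I rate it minor to moderate, as a correction of a stated figure. It does not show that the trial is underpowered; that question turns on the 220.

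**What to change.** Replace the sentence in {14} with a statement that 264 enrolled allows for a 16.7% loss and that with a 20% loss about 211 participants have observed 6-month data. Add the power at 211, naming the effect-size index and the numerator degrees of freedom. On the reading used here that is 82.4% for a 1-df effect or 67.1% for a 3-df comparison.

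The cost is one or two corrected sentences, with no change in enrolment.

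If the 220 is re-derived, divide the new figure by 0.80 and round up to a multiple of four. On the Cohen's f reading:
- 1 df: 265 / 0.80 = 331.25, so 332 (83 per arm).
- 3 df: 359 / 0.80 = 448.75, so 449, and 452 for equal arms (113 per arm).

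A changed total, unlike a corrected sentence, would mean enrolling more participants in a trial running since October 2021. The protocol sends important modifications to the ethics committee for approval.

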### Recruitment {15}

Recruitment is carried out online, through announcements in outpatient departments, and by telephone from the National Center for Standardized Metabolic Management (Chengdu, China). For the online recruitment announcement, health education nurses at the First Affiliated Hospital of Chengdu Medical College have sent recruitment information to a WeChat group of individuals with T2DM that is managed by the National Center. Recruitment advertisements have been posted on the bulletin boards of outpatient departments at the two study sites. Researchers are also contacting participants using the telephone numbers on record at the National Center.

## Assignment of interventions: allocation

### Sequence generation {16a}

Before enrollment began, two sets of random numbers were generated using EXCEL by people not involved in the study. The serial number of each set was determined in advance and placed in an opaque, sequentially numbered envelope. Upon completion of the baseline assessment, eligible participants will be randomly (proportionally) assigned to one of four groups.

### Concealment mechanism {16b}

Before enrollment began, people not involved in the study used Microsoft Word to generate two sets of random numbers, determined the serial number of each group in advance and put them in sequentially numbered opaque envelopes, and hid them from all personnel, including the investigators, field staff, and participants.

### Implementation {16c}

Recruitment will be conducted by researchers and assisted by doctors and nurses at both hospitals’ diabetes clinics. After the baseline assessment is completed, each participant will select an envelope, which will indicate his or her allocation to one of the four groups described above.

## Assignment of interventions: blinding

### Who will be blinded {17a}

We do not blind the evaluators of the result scale and physical examination but only group them after baseline data collection to avoid the impact of subjective bias on baseline data. In the subsequent result evaluation, the evaluators of the scale and physical examination are not blinded, only the laboratory testers of HbA_1c_ are blinded, and the data analysis personnel are not blinded either.

### Procedure for unblinding if needed {17b}

The design is open label with only HbA_1c_ tester being blinded so unblinding will not occur.

## Data collection and management

### Plans for assessment and collection of outcomes {18a}

All participants will complete baseline assessments and complete follow-up at the 3rd and 6th month after the intervention.

At baseline, demographic data will be collected on age, sex, ethnicity, educational level, marital status, employment status, current residence, and method of paying for medical expenses. Data will be collected on the following clinical variables: chronic complications related to diabetes, such as hypertension, cardiovascular disease, cerebrovascular disease, peripheral vascular disease, kidney disease, peripheral neuropathy, eye disease and diabetic foot. Any chronic complications of diabetes that arise during the study will be recorded at the 6th month. Similarly, data on acute complications related to diabetes will be collected at baseline, such as hypoglycemia and lactic acidosis or ketoacidosis; and current diabetes treatments, including non-drug therapy, oral hypoglycemic drugs, and insulin therapy. Any acute complications of diabetes that arise during the study will be recorded at the 6th month.

At baseline and again at the 6th month, all participants will be asked to fill out three questionnaires. In addition, the App and the App + Reminder groups will fill out a fourth questionnaire at 6th month, which assesses their satisfaction with the smartphone application and glucose meter (Table 2). At baseline and again at the 3rd and 6th month, data will be collected on height, weight, blood pressure and HbA_1c_. At the 3rd and 6th month, all participants will be asked about their frequency of blood glucose monitoring.

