### Outcomes {12}

Data are collected at three times, including two follow-up visits at baseline, the 3rd month after intervention, and the 6th month after intervention, through participant visits to the hospital by the investigator.

The primary outcome is the level of HbA_1c_, which reflects blood glucose levels over the preceding 2–3 months and is a good indicator of blood glucose control [10, 11]. All results will be made by high-performance liquid chromatography at the same certified external laboratory to ensure consistency.

Secondary outcomes include frequency of blood glucose monitoring, body mass index, blood pressure, knowledge about diabetes, health beliefs related to diabetes, and diabetes self-management behavior. The App and the App + Reminder groups will also be asked about their satisfaction with the smartphone application.

The following questionnaires will be used for the study:

Change in knowledge from baseline as measured by the Chinese version of the Diabetes Knowledge Questionnaire (DKN) [12]. Each item is scored from 0 to 1, and the total scores range from 0 to 23 (Higher score indicating greater knowledge of diabetes)Change in health belief from baseline as measured by the Health Belief Questionnaire (HBQ) [13]. Scores ranging between 20 to 100 (higher score indicating better outcomes)Change in self-management behavior from baseline as measured by the Type 2 Diabetes Self-management Behavior Scale (2-DSCS) [14]. Total scores range from 26 to 130 (higher score indicating better outcomes)Custom-made questionnaire to assess user satisfaction with Dnurse application and its paired glucose meter. Participants who use the APP 6 months after the intervention will complete the assessment. The 5-level Likert scoring method is adopted, and the total scores range from 11 to 55 points (Table 2)

**Table 2 Tab2:** Custom-made questionnaire to assess user satisfaction with Dnurse application

Item	Very satisfied	Satisfied	Neither satisfied nor dissatisfied	Slightly dissatisfied	Very dissatisfied
1. Your satisfaction with the application interface					
2. Your satisfaction with the application’s ease of use					
3. Your satisfaction with how the application records blood glucose					
4. Your satisfaction with the health information provided by the application					
5. Your satisfaction with using the application to manage diabetes					
6. Your satisfaction with the application’s safety					

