### Data management {19}

The data will be managed in accordance with the requirements established by law. All data collected will be identifiable so that participants can be contacted. During the recruitment process, each participant is given a unique study identification number. Participants will complete an online questionnaire using the Questionnaire Star (https://www.wjx.cn/), and the data of the Questionnaire Star will be authenticated and recorded over a secure network connection. All other information about the participants will be stored in a secure, password-protected computer.

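### The carry-forward rule scores everyone without a month-6 DKN, HBQ or 2-DSCS score as exactly zero change, which biases three secondary outcomes

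*Protocol article*

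**What the plan says.** - **Schedule.** Section {18a} of the protocol article states: "At baseline and again at the 6th month, all participants will be asked to fill out three questionnaires". Table 1 agrees: the row for DKN, HBQ and 2-DSCS is marked at baseline and 6 months and is empty at 3 months. HbA1c, weight and blood pressure are marked at all three times.
- **Form of the outcome.** Outcomes {12} defines each of the three scales as a change from baseline.
- **Missing data.** Section {20c} gives a general rule, "Missing values are filled with the last data", and then two examples. The second reads: "For participants with 3rd month follow-up but without 6th month follow-up, the 3rd month data will be filled in".
- **Expected loss.** Sample size {14} arrives at 264 participants after an allowance introduced as "To compensate for an estimated 20% loss to follow-up".
- **Route of collection.** Outcomes {12} describes data collection "through participant visits to the hospital by the investigator". Data management {19} adds: "Participants will complete an online questionnaire using the Questionnaire Star". It does not say which questionnaires are on that platform.

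**The concern.** Last-value filling is usually discussed for outcomes measured repeatedly, where the filled value at least reflects some time on the intervention. Here the three scales have one post-baseline time point. When it is missing, the only value to carry forward dates from before the intervention began. The rule therefore asserts that every such participant learned nothing, changed no belief and altered no behaviour, including those seen at month 3 and known to be still in the trial.

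Two consequences follow. If the App or the reminders work, the estimated difference shrinks in proportion to the loss. If participants improve in every arm and loss is unequal, a difference appears that no intervention caused. Unequal loss is plausible in this design: it is open label, only two arms receive weekly calls, and only two have the app and its linked meter.

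**Working it through.** **Inputs.** From Sample size {14}: total 264 and loss 20%. The plan's own inflation is 220 × 1.2 = 264. From Study design {8}: four equal groups, so 264/4 = 66 per arm and 132 on each side of the App comparison. I assume that the 20% is the share without a month-6 score.

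**1. Number affected.** 264 × 0.20 = 52.8, about 53. Per arm, 66 × 0.20 = 13.2, about 13.

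**2. Equal loss.** Let d be the proportion without a month-6 score, and suppose they would have changed as completers did. The filled mean change in an arm is (1 − d) × true change + d × 0, so a true difference D is estimated as (1 − d) D:
- d = 10%: 0.90 D
- d = 20%: 0.80 D
- d = 30%: 0.70 D

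As an illustration, take D = 0.40 SD. This is the plan's effect size of 0.2 read as Cohen's f for two equal groups; the plan states no effect for the scales. The estimates are 0.36, 0.32 and 0.28 SD.

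**3. Unequal loss, no true effect.** Every arm improves by m. The filled difference, App minus no App, is (1 − d_App) m − (1 − d_noApp) m = (d_noApp − d_App) m. The documents give no loss by arm. For a gap of 5 to 20 percentage points (assumption), the false difference is 0.05 m to 0.20 m. It favours the App if the App arms lose fewer people and counts against it if they lose more.

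**4. Unequal loss, true effect.** Assume true changes of 0.6 SD (App) and 0.2 SD (no App), a true difference of 0.40:
- Loss 10% App, 20% no App: 0.6 × 0.9 − 0.2 × 0.8 = 0.38
- Loss 20% App, 10% no App: 0.6 × 0.8 − 0.2 × 0.9 = 0.30

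**5. Precision and power**, in SD of the change score, equal 20% loss, mean change near zero:
- Completers only, n = 264 × 0.8 ≈ 211: SE = 2/√211 = 0.138
- Zero-filled, n = 264: SE = √0.8 × 2/√264 = 0.110
- 0.8 × 0.138 = 0.110, so the estimate and its standard error shrink by the same factor.

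The ratio of estimate to standard error hardly changes: 0.32/0.110 = 2.91 against 0.40/0.138 = 2.90. Power is about 0.82 to 0.83 either way, against about 0.90 with complete data. What moves is the centre of the interval: a shift of 0.08 SD is 0.08/0.110 = 0.73 standard errors, and a nominal 95% interval then covers the true 0.40 about 89% of the time.

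**The case against.** **The fill rule works, and the month-3 sentence is only an example.** This stands. A reader might infer that the rule cannot operate for these scales because there is no month-3 score. The text does not support that: the general sentence in {20c} applies, and the last available value is the baseline score. The trouble is what the rule yields.

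**The interval is not falsely narrow.** This also stands. Comparing 0.110 with 0.138 tempts one to say that filling invents precision. But 0.110 is the correct standard error of the shrunken estimate, so calling the interval too narrow would count the same shrinkage twice.

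**The missing scores may not be avoidable.** Because the questionnaire is online while data are gathered at visits, a reader might infer that non-attenders are never asked and that most of the loss could be prevented with a link. The article neither provides for remote completion nor forbids it. Chasing procedures are commonly left to the full protocol, and people who have withdrawn or cannot be reached may not answer.

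**Home completion has its own bias.** DKN is a knowledge test, the App arms have disease information on their phones, and the trial is open label. Unsupervised answers could favour the App. This is a fair point and is why remote completion is optional below.

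**Only secondary outcomes are touched, and the sizes depend on assumptions.** Both are true. HbA1c has a month-3 value. The per-arm loss figures are illustrative. The zero change itself rests on no assumption; it follows from the schedule and the rule. An analysis plan faithful to {20c} would inherit it, so this is not a detail the article merely omits.

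**Conclusion.** The point holds as a defect of {20c} for DKN, HBQ and 2-DSCS. Every participant without a month-6 score enters with a change of exactly zero, about 53 of 264 at the planned 20% loss. With equal loss, and missing participants who would have changed like completers, the estimate is 0.80 D (0.90 D to 0.70 D for 10% to 30% loss). With unequal loss the direction of bias cannot be known in advance; for an assumed gap of 5 to 20 points, a false difference of 0.05 m to 0.20 m arises where there is no effect.

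The shrinkage factor would differ if those lost would in truth have changed less than completers, and it would vanish only if the intervention had no differential effect on them. The documents do not support saying that the rule is inoperable, that standard errors are wrong, that power suffers beyond the loss of the participants themselves, or that the missing scores are largely preventable. The matter deserves correction but does not touch the primary outcome.

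**What to change.** In {20c}, exclude DKN, HBQ and 2-DSCS from the last-value fill. Analyse observed month-6 scores with the baseline score as covariate, or use multiple imputation by arm. Keep the baseline fill as a sensitivity analysis and label it as assuming no change. Section {20a} already puts baseline values in its models, so the amendment is short and needs no new data.

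The cost is that the main analysis then relies on missing scores being missing at random given arm and baseline, and its intervals are somewhat wider (standard error 0.138 against 0.110 SD in the example above).

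Optional: if the three scales are already on the online platform, invite non-attenders to complete them remotely at month 6 within a fixed window, and record where each was completed. Section {19} suggests this is feasible: "All data collected will be identifiable so that participants can be contacted". The yield is unknown. If 25% to 75% responded (assumption), the share without a score would fall from 20% to 20% × 0.75 = 15% or 20% × 0.25 = 5%. The gain should be weighed against home completion of the knowledge test and the mixing of settings in a trial that began in October 2021.
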